### Treatment

All chemotherapeutic agents are SOC treatments and will be administered as per local policy in terms of patient assessment, chemotherapy dose and frequency. Dose reductions due to toxicity or dihydropyrimidine dehydrogenase (DPYD) mutations will take place according to local hospital guidelines. The use of raltirexed will be accepted in the context of cardiotoxicity.

#### Arm A: SOC ACT

Patients randomised to SOC chemotherapy will be recommended 3 months of CAPOX or 6 months of capecitabine monotherapy by their clinician depending on histopathological features of their resected tumour and clinical situation. Post-operative (Month 0) and serial blood samples for ctDNA will be biobanked and processed at a future date. Patients in the SOC arm will not receive ctDNA results in real time.

#### Arm B: ctDNA guided ACT

For patients randomised to ctDNA guided ACT, the post-operative (Month 0) blood sample will be processed in real time and the result will be published on the Guardant Health online portal. The recommended SOC chemotherapy regimen will continue to be used in patients who are ctDNA positive post-operatively, whilst ACT will be de-escalated in those who are ctDNA negative. Where 3 months of CAPOX has been recommended, treatment will be de-escalated to 3 months of capecitabine alone, and where 6 months of capecitabine monotherapy has been recommended, treatment will be de-escalated to no chemotherapy. Patients who are ctDNA negative post-operatively and have their chemotherapy de-escalated (Fig. 2) will undergo a further blood test for ctDNA post-ACT or 3 months after the post-operative sample in those who are not receiving ACT. Patients who remain ctDNA negative at the post-ACT (Month 3) timepoint will continue to follow up. If ctDNA becomes positive, chemotherapy will be escalated to 3 months of CAPOX in all patients. A CT scan will also be performed to rule out radiological macroscopic disease.

**Fig. 2 Fig2:**
[figure not shown]
De-escalation/escalation strategy in ctDNA negative group in the ctDNA-guided arm

#### Follow up

Eligible patients will continue treatment unless there is evidence of recurrent disease, unacceptable toxicity or withdrawal of consent from the study. Following completion of adjuvant treatment, patients will undergo longitudinal blood tests for ctDNA every 3 months for the first year post-surgery, every 6 months for years 2 and 3, and annually for years 4 and 5, with computer tomography (CT) imaging performed at the end of years 1, 2 and 3 (Fig. 3). Patients will be followed up for a total of 5 years. In the instance of disease relapse, a blood sample will be taken 2–8 weeks after clinical or radiological confirmation of recurrent disease. Patients will continue follow up in the clinical trial as outlined until death, discharge from routine follow up (5 years), or withdrawal from the study. Patients whose disease recurs will be followed up for survival annually but no further blood samples will be collected.

**Fig. 3 Fig3:**
[figure not shown]
Follow up schedule for blood sample collection and CT imaging

#### ctDNA assay

In collaboration with Guardant Health, we will use the Guardant Reveal ctDNA assay to analyse blood samples. The Guardant Reveal assay is the first and only blood-based tumour-naïve ctDNA assay to detect MRD in early CRC. It leverages several technical advances in ctDNA detection to improve assay sensitivity without requiring a priori knowledge of the tumour genotype. The technique combines genomic and methylation features with independent analyses occurring in parallel to increase sensitivity. It has a turnaround time of 7–14 days for results processed in real time for clinical use. It is Clinical Laboratory Improvement Amendments (CLIA) certified and was approved by the Food and Drug Administration (FDA) in March 2021, and is already in use in three global interventional clinical trials [18–20]. Blood samples taken at the post-operative (Month 0), post-ACT (Month 3), longitudinal and relapse timepoints up to 24 months will be analysed in the first instance. Only post-operative and, if negative, post-ACT (Month 3) blood samples in patients randomised to the ctDNA-guided arm will be analysed in real time, with the remaining samples being bio-banked for future analysis.

### Quality of life and health economic analysis

Quality of life and cost-effectiveness of treatment will be assessed at each time point during the study, i.e., at baseline, post-operatively, every 3 months for year 1, every 6 months for years 2 and 3, and annually for years 4 and 5. Quality of life data related to chemotherapy-induced peripheral neuropathy will be collected using the FACT/GOG-Ntx4 subscale. Additional quality of life data will be collected using European Organisation for Research and Treatment of Cancer Quality of Life Questionnaire (EORTC QLQ-C30), the Colorectal Cancer-Specific Quality of Life Questionnaire (QLQ-CR29) and the EuroQoL 5-Dimension 5-Level (EQ-5D-3L) subscale. A pilot will be undertaken on 40 patients to assess the frequency with which questionnaires are successfully completed, with a view to adapt the frequency and length of the RUtINE™ questionnaire should the response rate be low.

### Study endpoints

#### Primary endpoint

The primary endpoint is the difference in DFS at 3 years between the ctDNA-guided arm and the SOC arm. DFS is measured from the time of surgery to recurrence, death from any cause or censored from the last follow up. Recurrence will be based on investigator assessment of clinical or radiological evidence of disease relapse. The analysis population will include all patients treated on the study. The primary population for analysis will be the Intent to Treat (ITT) population, defined as all patients randomised to treatment arms; SOC chemotherapy or ctDNA guided ACT. A sensitivity per protocol analysis will also be performed defined as all those receiving treatment as planned per randomisation.

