## Abstract

**Background:**

Circulating tumour DNA (ctDNA) to detect minimal residual disease (MRD) is emerging as a biomarker to predict recurrence in patients with curatively treated early stage colorectal cancer (CRC). ctDNA risk stratifies patients to guide adjuvant treatment decisions. We are conducting the UK’s first multi-centre, prospective, randomised study to determine whether a de-escalation strategy using ctDNA to guide adjuvant chemotherapy (ACT) decisions is non-inferior to standard of care (SOC) chemotherapy, as measured by 3-year disease free survival (DFS) in patients with resected CRC with no evidence of MRD (ctDNA negative post-operatively). In doing so we may be able to spare patients unnecessary chemotherapy and associated toxicity and achieve significant cost savings for the National Health Service (NHS).

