Currently considerations regarding the need for ACT include histopathological features of the resected tumour and other patient factors such as age, comorbidities, PS and patient preference, leading to shared decision making. ctDNA has emerged as a biomarker for minimal residual disease (MRD) and can predict early relapse, offering a tailored approach to individual decision making [14]. Stage II patients who are ctDNA negative post-operatively have been shown to have a 3 year recurrence free survival (RFS) of 90% compared to 0% in those who are ctDNA positive [15]. Similarly in stage III disease 3 year RFS is 76% and 47% respectively [16]. Recent data from an observational registry, suggests that ACT in patients who are ctDNA negative makes little difference to DFS [17] and is potentially exposing patients to unnecessary toxicity which could be safely avoided. By reducing or omitting needless treatment in post-operative ctDNA negative patients, they may be spared the short and long-term side effects of treatment, multiple hospital visits, as well as the potential psychological impact of treatment. Should this study be positive and adopted into standard practice, there could be huge cost-saving implications for the National Health Service (NHS).

We hypothesise that ACT decisions guided by the post-operative ctDNA result will enable biomarker driven selection of patients who would and would not benefit from ACT, and thereby reduce the proportion of patients receiving ACT without compromising DFS. The primary objective is to demonstrate that a de-escalation strategy of ctDNA guided adjuvant chemotherapy is non-inferior to SOC chemotherapy as measured by 3 year DFS in patients with high risk stage II or stage III resected CRC with no evidence of MRD (i.e., those who are ctDNA negative post-operatively).

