### Statistical analysis and sample size

The 3 year DFS in the SOC arm is expected to be 75%. To demonstrate non-inferiority in survival with a power of 80%, alpha of 10% (2-sided), and non-inferiority hazard ratio of 1.25 (ruling out 69.8% 3-year DFS), a sample size of 810 patients in each arm is estimated with a total of 530 events required for the analysis. As per the statistical design, 1621 patient are required to be recruited and randomised (approximately 810 per arm). Accrual will take place over 4 years across approximately 50 UK sites. An Independent Data Monitoring Committee (IDMC) will meet regularly to review the data, and particularly with regards to safety and futility. Any decision by the IDMC to discontinue the trial due to lack of efficacy will endorsed by the Trial Steering Committee (TSC).

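### The primary objective concerns ctDNA-negative patients, but the 1.25 margin is tested in all randomised patients, which makes it looser than 1.25 for the objective as worded

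*Protocol article*

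**What the plan says.** The last paragraph of the Introduction sets the objective: "The primary objective is to demonstrate that a de-escalation strategy of ctDNA guided adjuvant chemotherapy is non-inferior to SOC chemotherapy", measured by 3-year DFS, in patients "with no evidence of MRD (i.e., those who are ctDNA negative post-operatively". The abstract's Background carries the same restriction: "in patients with resected CRC with no evidence of MRD (ctDNA negative post-operatively".

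The Primary endpoint section compares the whole ctDNA-guided arm with the whole SOC arm: "The primary population for analysis will be the Intent to Treat (ITT) population, defined as all patients randomised to treatment arms". The Statistical analysis and sample size section expects 75% 3-year DFS in the SOC arm and sets a "non-inferiority hazard ratio of 1.25 (ruling out 69.8% 3-year DFS", with 530 events and 1621 randomised. It makes no allowance for ctDNA status.

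In the ctDNA-guided arm, "The recommended SOC chemotherapy regimen will continue to be used in patients who are ctDNA positive post-operatively"; only negatives are de-escalated. In the SOC arm, "Post-operative (Month 0) and serial blood samples for ctDNA will be biobanked and processed at a future date".

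**The concern.** The article names two target populations for one primary question. Only ctDNA-negative patients are planned to be treated differently by arm. Positives contribute no planned contrast, yet the Introduction gives them much the worse prognosis (3-year RFS 0% in stage II and 47% in stage III, against 90% and 76% in negatives). They therefore supply a disproportionate share of events and draw the overall hazard ratio towards 1. In a non-inferiority trial that is the direction that favours success.

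A result reported as non-inferior at 1.25 would naturally be read as answering the objective in the Introduction. In the patients that objective names, the test would have excluded only a larger hazard ratio. Those are the patients whose chemotherapy would be reduced or omitted on the strength of the result.

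**Working it through.** **The plan's own figures.** The margin conversion reproduces: 0.75^1.25 = 0.698. The Schoenfeld event count at a hazard ratio of 1.25, two-sided 10% and 80% power is 4(1.645 + 0.842)²/(ln 1.25)² ≈ 497. The stated 530 is about 6% higher and gives 82% power. That discrepancy is on the safe side and does not affect this point.

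**Inputs from the article.** SOC 3-year DFS 75%; margin 1.25; 530 events; one-sided 5% (10% two-sided); 3-year RFS by ctDNA status and stage as above.

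**Assumptions.** RFS stands in for DFS. The hazard ratio in positives is 1, because the planned regimen is the same. The positive share p is the same in each stage. The stage III share m is not given, so 50–80% is shown. Separately, p = 20% with DFS of 40–50% in positives is shown.

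**Formulas.**
- SOC DFS in negatives: S = 0.76m + 0.90(1 − m). DFS in positives: q = 0.47m + 0 × (1 − m).
- Positive share from 0.75 = pq + (1 − p)S, so p = (S − 0.75)/(S − q). Where p and q are assumed directly, S = (0.75 − pq)/(1 − p).
- At the margin, with positives unchanged: S′ = (0.698 − pq)/(1 − p). Hazard ratio in negatives = ln S′/ln S.
- Share of 3-year events in positives: p(1 − q)/0.25. Events in negatives, E = 530 × (1 − that share). Power there = Φ(√(E/4) × ln 1.25 − 1.645).
- If the true hazard ratio in negatives is 1.25, the all-randomised value is HR_all = ln[pq + (1 − p)S^1.25]/ln 0.75. Chance of passing = Φ(√(530/4) × ln(1.25/HR_all) − 1.645).

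**Worked case, m = 0.6.** S = 0.816 and q = 0.282, so p = 0.066/0.534 = 12.4%. Positives supply 0.124 × 0.718/0.25 ≈ 35.5% of events. S′ = (0.698 − 0.035)/0.876 = 0.757, and the hazard ratio in negatives is ln 0.757/ln 0.816 = 1.37. Events in negatives are 342, giving 66% power. HR_all = ln 0.7146/ln 0.75 = 1.168, and the chance of passing is 19%.

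| Scenario | p | q | HR in negatives at the all-randomised margin | Events in negatives (of 530) | Power in negatives | Chance of passing if HR in negatives is 1.25 |
|---|---|---|---|---|---|---|
| 80% stage III | 9.2% | 37.6% | 1.32 | 408 | 72.9% | 12.5% |
| 60% stage III | 12.4% | 28.2% | 1.37 | 342 | 66.2% | 19% |
| 50% stage III | 13.4% | 23.5% | 1.40 | 312 | 62.8% | 23% |
| Assumed | 20% | 50% | 1.40 | 318 | 63.5% | 23% |
| Assumed | 20% | 40% | 1.46 | 276 | 58.2% | 29% |
| Assumed | 10% | 47% | 1.31 | 418 | 73.7% | 12% |

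**Cross-check.** With q = 47% and p = 10%, 15% and 20%, an event-weighted log hazard ratio gives 14%, 20% and 29% for the last column. A Cox simulation of 300 runs per setting, with about 630–650 events, gives 10%, 19% and 25%. The methods agree on direction and rough size.

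**The case against.** The strongest reply is that patients are randomised to a strategy, so comparing everyone randomised is the valid estimand for it. The abstract's Methods and Discussion, the Study design section and the article's Discussion all word the question that way, and the endpoint and sample size match them. The ctDNA-negative restriction appears only in the abstract's Background and the Introduction. All of this stands, and it is why the remedy keeps the all-randomised test. It does not remove the conflict, because the sentence labelled as the primary objective carries the restriction. An analysis plan that is not shown could not change what the 1.25 margin excludes in negatives.

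Three stronger readings are tempting, and the document does not support them.
- *The primary test has an inflated type I error.* It does not. The nominal 5% holds at an all-randomised hazard ratio of 1.25. With 1.25 in negatives only, the all-randomised value is truly smaller, and passing is correct for the strategy question. The excess is an error only for the objective as worded.
- *No analysis in ctDNA-negative patients is planned.* The article lists none, but it condenses a fuller protocol and may be accompanied by an analysis plan. Absence here proves nothing.
- *The size of the dilution is known.* It is not. The positive share is not stated, the RFS figures come from separate cited cohorts, and the article does not say whether the positives in them received chemotherapy. The 0% in stage II may overstate the event share of positives in this trial.

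A second confirmatory test at 1.25 in negatives would also be a design choice, not a correction: its power is below 80% and it would need a place in the testing order.

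**Conclusion.** Wrong as written. The stated primary objective and the primary analysis address different populations, and the difference favours a non-inferior conclusion for the objective. The contradiction and its direction follow from the text, given that the planned regimen for positives is the same in both arms. The size rests on assumptions. Under the article's RFS values with 50–80% stage III (implied positive share 9–13%), the margin corresponds to about 1.32–1.40 in negatives; with 20% positive and 40–50% DFS in positives, about 1.40–1.46. A true 1.25 in negatives passes about 12–29% of the time across these scenarios. The dilution grows with the positive share and with worse prognosis in positives. This is not a case against the all-randomised analysis; it limits what that analysis can be said to show.

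**What to change.** - Keep the all-randomised ITT comparison as the primary test of the ctDNA-guided strategy, and reword the objective in the abstract's Background and in the Introduction to match.
- Pre-specify, in the Primary endpoint section or beside it, a key secondary DFS comparison by randomised arm among patients ctDNA negative at Month 0 in both arms, placed after the ITT test. Assay the stored SOC samples blind to outcome, and report missing or failed assays by arm.
- Rest any claim about ctDNA-negative patients on that comparison only.
- State the hazard ratio in negatives that the all-randomised margin implies and the power available there (about 58–74% at 530 total events, depending on the positive share and prognosis), with the assumed positive share made explicit.

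The cost is protocol and analysis-plan wording. Month 0 samples are already planned in both arms, and the SOC samples are due to be processed later. The downside is that the stated power for the ctDNA-negative question falls below 80%.

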#### Secondary endpoints

The proportion of patients in the ctDNA guided arm receiving SOC ACTThe proportion of patients in the ctDNA guided arm who are ctDNA negative post-operatively who become ctDNA positive during follow up and receive chemotherapy as an escalation of treatmentThe difference in overall survival (OS) between the two arms, measured from the time of randomisation to death from any causeThe difference in neurotoxicity between the two arms, with data based on FACT/GOG-Ntx4 and common terminology criteria of adverse events (CTCAE) version 5The difference in quality of life between the two arms, with data based on EORTC QLQ-C30 and CR29 and EQ-5D-3LThe cost-effectiveness of ctDNA guided arm compared to the SOC arm, with data based on a dedicated health economic questionnaire (RUtINE.™)

### Data collection and management

The Royal Marsden MACRO database will be used for clinical data collection and recording of anonymised patients and central management of the data. This may be initially via case report forms (CRFs). All staff will be trained to use the software appropriately prior to involvement in the study. As far as possible, any missing or incongruous data fields will be chased with sites for data input or clarification.

### Statistical analysis and sample size

The 3 year DFS in the SOC arm is expected to be 75%. To demonstrate non-inferiority in survival with a power of 80%, alpha of 10% (2-sided), and non-inferiority hazard ratio of 1.25 (ruling out 69.8% 3-year DFS), a sample size of 810 patients in each arm is estimated with a total of 530 events required for the analysis. As per the statistical design, 1621 patient are required to be recruited and randomised (approximately 810 per arm). Accrual will take place over 4 years across approximately 50 UK sites. An Independent Data Monitoring Committee (IDMC) will meet regularly to review the data, and particularly with regards to safety and futility. Any decision by the IDMC to discontinue the trial due to lack of efficacy will endorsed by the Trial Steering Committee (TSC).

### Planned recruitment

With a target recruitment of 1621 patients and recruitment ongoing for 4 years, at least 34 patients will need to be recruited per month. We plan to activate up to 50 UK sites, many of which are already participating in our TRACC Part B observational study. Therefore, at least 1–2 patients would need to be recruited at each site per month on average, once all sites are open. We anticipate this recruitment target is achievable given the prevalence of this tumour type and stage in the UK.

## Discussion

We describe the protocol of the multi-centre, prospective, randomised trial designed to compare the 3 year DFS in patients with high risk stage II and stage III fully resected colon and rectal cancers treated with ctDNA guided ACT versus SOC chemotherapy, sponsored by the Royal Marsden Hospital NHS Foundation Trust, London. The study builds on the results from TRACC Part B; the observational, prospective, translational research study involving serial blood sampling for ctDNA pre- and post-operatively, which demonstrated an improved 12 and 24 month RFS in patients who were ctDNA negative post-operatively.

TRACC Part C is the only ctDNA-guided study of ACT in CRC running in the UK and addresses a research question with significant health economic importance. The DYNAMIC II study is the only reported study in this space to date globally, which provided evidence to support the de-escalation of ACT in patients with resected stage II colon cancer [21]. We anticipate that the results of this study, together with the DYNAMIC II study and similar ongoing studies across the world will generate the evidence to support the clinical utility of ctDNA in the MRD de-escalation setting, generating support for a change to standard practice. In doing so, it may spare patients unnecessary chemotherapy and its associated toxicities and saeg the health service significant costs, redirecting resources elsewhere. The use of chemotherapy in this setting may halve.

TRACC Part C is one of the only ctDNA-guided studies using a plasma-only tumour-naïve ctDNA assay for MRD detection in CRC globally. Utilising a blood-only assay with a turnaround time of 7-14 days, where analysis of tumour tissue is not required, lends itself to a more streamlined approach to recruitment within the study, as well as smooth potential future implication into standard clinical practice. The inbuilt patient reported outcomes (PROs), health economic analysis and process evaluation will provide a route to effective implementation in SOC clinical practice within the NHS and elsewhere in the future.

## Data Availability

Data sharing not applicable as no datasets generated and/or analysed for this study to date.

## Abbreviations

ACT: Adjuvant chemotherapy
CAPOX: Capecitabine and oxaliplatin
CEA: Carcinoembryonic antigen
CI: Confidence interval
CRC: Colorectal cancer
CRF: Case report form
CT: Computer tomography
ctDNA: Circulating tumour DNA
DFS: Disease free survival
DPYD: Dihydropyrimidine dehydrogenase
EORTC: European organisation for research and treatment of cancer
FOLFOX: 5-Fluorouracil and oxaliplatin
FP: Fluoropyrimidine
IDMC: Independent Data Monitoring Committee
MRD: Minimal residual disease
NHS: National health service
OS: Overall survival
PS: Performance status
REC: Research ethics committee
RFS: Recurrence free survival
SOC: Standard of care
TNT: Total neo-adjuvant treatment
TSC: Trial Steering Committee
